### Instruments

Patients will be assessed at baseline, post-treatment (18 weeks after baseline), and at 3- and 12-month follow-ups. Scores on anxiety, depression and negative and positive affect will also be obtained after each module has been completed. The study variables and assessment times are summarized in Table 3.

**Table 3 Tab3:** Study variables and assessment points

Instrument	Assessment area	Time of assessment
MINI Neuropsychiatric	Psychiatric diagnosis	Baseline, Post-T and follow-ups
Interview		
BAI	Severity of anxiety	Baseline, Post-T and follow-ups
BDI-II	Severity of depression	Baseline, Post-T and follow-ups
Sociodemographic data	Gender, age, marital status, education, occupation, economic level	Baseline
OASIS	Severity of anxiety	Post-module
ODSIS	Severity of depression	Post-module
SIAS	Severity of SAD symptoms	Baseline, Post-T and follow-ups
PDSS-SR	Severity of PD and agoraphobia symptoms	Baseline, Post-T and follow-ups
PSWQ	Severity of GAD symptoms	Baseline, Post-T and follow-ups
OCI-R	Severity of OCD symptoms	Baseline, Post-T and follow-ups
EQ-5D	Health-related quality of life	Baseline, Post-T and follow-ups
PANAS	Positive and negative affect	Post-module
BIS-BAS	Behavioral inhibition/activation	Baseline, Post-T and follow-ups
ETS	Expectation of treatment	Baseline
OTS	Opinion of treatment	Post-T

Post-T, post-treatment (18 weeks after baseline); follow-ups, 3- and 12-month follow-ups. BAI, Beck Anxiety Inventory; BDI-II, Beck Depression Inventory-II; OASIS, Overall Anxiety Severity and Impairment Scale; ODSIS, Overall Depression Severity and Impairment Scale; SIAS, Social Interaction Anxiety Scale; PDSS-SR, Self-Reported Panic Disorder Severity Scale; PSWQ, Penn State Worry Questionnaire; OCI-R, Obsessive-Compulsive Inventory-Revised; EQ-5D, EuroQoL-5D questionnaire PANAS, Positive and Negative Affect Scale; BIS-BAS, Behavioral Inhibition and Behavioral Activation Scales; ETS, Expectation of Treatment Scale; OTS, Opinion of Treatment Scale

#### Diagnosis interview

Mini International Neuropsychiatric Interview Version 5.0.0 (MINI) [79]. It is a short structured diagnostic psychiatric interview that yields key DSM-IV and ICD-10 diagnoses. The MINI can be administered in a short period of time, and clinical interviewers need only brief training. The MINI has been translated into Spanish and validated [80].

#### Primary outcomes

Beck Anxiety Inventory (BAI) [81]. The BAI is a 21-item self-report measure designed to assess anxiety, with a maximum of 63 points. Each item has a four-point severity scale (for example, not at all, mildly, moderately, and severely) that addresses symptoms experienced during the past week. The internal consistency of the BAI has been found to range from .85 to .94, and it has shown adequate convergent and divergent validity. The Spanish version of the BAI has shown high internal consistency (α = .93) [82].

Beck Depression Inventory (BDI-II) [83]. It is one of the most widely used questionnaires to evaluate depression severity in pharmacological and psychotherapy trials. It consists of 21 items about the different symptoms characterizing major depression disorder, added together to obtain the total score, which can be a maximum of 63 points. The instrument has good internal consistency (α = 0.76 to 0.95). The Spanish version of this instrument has also shown a high internal consistency (α = 0.87) for both the general and clinical populations (α = .89) [84].

#### Secondary outcomes

##### Sociodemographic variables

The following sociodemographic variables will be collected: gender, age, marital status (single, married/relationship, separated/divorced, and widowed), education (years of education), and work status.

##### Diagnosis-specific measures

In order to evaluate the specific anxiety disorder shown by each participant, four different instruments will be implemented. One of the four following questionnaires will be selected and included at pre, post-treatment, and 3- and 12-month follow-up assessments, depending on the main diagnosis given to each participant.

SAD: Social Interaction Anxiety Scale (SIAS) [85]. This scale is made up of twenty items rated from 0 to 4 that assess the anxiety experienced by the patient in social interaction situations. The scale has good internal consistency (α = .88 to .94), good test-retest and discriminant reliability, and appropriate construct validity. The Spanish validation showed adequate internal consistency and good construct validity [86].

PD/A: Self-Reported Panic Disorder Severity Scale (PDSS-SR) [87]. The scale evaluates the severity of the PD symptomatology through measures of panic attack frequency, distress during panic attacks, anticipatory anxiety, fear and agoraphobic avoidance, fear and avoidance of physical sensations, and work and social impairment. Scale reliability (α = .917) and test-retest reliability (ICC = .81) were shown to be excellent. The psychometric analysis of the Spanish version showed excellent internal consistency (α = .85), good test-retest reliability, and adequate convergent validity [88].

GAD: Penn State Worry Questionnaire (PSWQ) [89], which evaluates worry as an uncontrollable, generalized and excessive experience. The PSWQ has good psychometric properties, with an internal consistency ranging from .91 to .95, and good validity and test-retest reliability. The Spanish version of the scale showed an internal consistency of .90 and a test-retest reliability of .82, as well as adequate convergent and discriminant validity [90].

OCD: Obsessive-Compulsive Inventory-Revised (OCI-R) [91]. The OCI-R is a scale made up of 18 items rated from 1 to 4 and organized in six dimensions (washing, verification, order, obsession, hoarding and mental neutralization) that assess obsessive-compulsive behaviors. The OCI-R has showed good internal consistency (α = .81 to .93), good to excellent test-retest reliability (α = .57 to .91) and good convergent validity. The internal consistency of the Spanish version of the OCI-R has been found to be good (α = .86) [92].

##### N/BI and E/BA

Behavioral Inhibition and Behavioral Activation Scales (BIS/BAS) [93]. These scales were designed to assess two temperaments identified in Gray’s biobehavioral theory of emotion [94], namely, behavioral inhibition and behavioral activation. The scale is made up of 20 items rated from 1 to 4, with seven BIS subscale items that evaluate individuals’ emotional responses to impending negative events and 13 BAS items that assess individuals’ behavioral and emotional responses to potentially positive events. The BIS/BAS have demonstrated good reliability in a large sample of individuals with emotional disorders (α = .73 to .92), and stronger associations with other measures of temperament (that is, neuroticism/negative affect and extraversion/positive affect, respectively) than with measures of anxiety or depressive disorder constructs, suggesting that they have good convergent and discriminant validity as indicators of temperament [95]. The internal consistency of the Spanish version ranges between .65 and .82 [96].

##### Post-module measures

Overall Anxiety Severity and Impairment Scale (OASIS) [97]. The OASIS consists of a 5-item questionnaire, rated from 0 to 4, that assesses the frequency and severity of the anxiety symptoms. The instrument also provides measures of avoidance, as well as work, academic, social and everyday life impairment related to anxiety symptoms. A psychometric analysis of the OASIS scale found good internal consistency (α = .80), test-retest reliability (k = .82) and convergent validity for this instrument.

Overall Depression Severity and Impairment Scale (ODSIS) [98]. The ODSIS is a self-report measure with five items that evaluate experiences related to depression. The ODSIS measures the frequency and severity of depression, as well as the level of avoidance, work/school/home interference, and social interference associated with depression. The internal consistency of the scale has been shown to be excellent, with a Cronbach's alpha between .91 and .94 and good convergent and discriminant validity. The Spanish psychometric properties of both the OASIS and the ODSIS are being studied by members of our research team at the time of the publication of this paper.

Positive and Negative Affect Scale (PANAS) [99]. The PANAS consists of 20 items that evaluate two independent dimensions: positive affect (PA) and negative affect (NA). The range for each scale (10 items on each) is from 10 to 50. The Spanish version has demonstrated high internal consistency (α = 0.89 and 0.91 for PA and NA in women, respectively, and α = 0.87 and 0.89 for PA and NA in men, respectively) in college students [100].

##### Quality of life

EuroQoL-5D questionnaire (EQ-5D) [101]. It is a generic instrument that measures health-related quality of life and consists of two parts: Part 1 assesses self-reported problems in each of five domains: mobility, self-care, daily activities, pain/discomfort and anxiety/depression. Each domain is divided into three levels of severity corresponding to no problems, some problems, and extreme problems, yielding a population-based preference score or societal index (SI). A total of 243 theoretically possible health states can be obtained, and the SI is calculated on the basis of these health states. Values range from 1 (best health state) to 0 (death). However, this index may also provide negative values that correspond to health states perceived as worse than death. Utility scores for these health states were assigned using readily available Spanish population tariffs [102]. Part 2 records the subject's self-assessed health on a visual analogical scale (VAS), a 10 cm vertical line on which the best and worst imaginable health states score 100 and 0, respectively.

##### Treatment expectations and treatment opinion

Expectation of Treatment Scale (ETS) and Opinion of Treatment Scale (OTS). These questionnaires are adapted from Borkovec and Nau [103]. The content of the six items, rated on a scale from 0 to 10, cover how logical the treatment seemed, to what extent it could satisfy the patient, whether it could be used to treat other psychological problems, its usefulness for the patient’s specific problem, and to what extent the treatment could be aversive. The expectation scale is applied once the treatment rationale has been explained, at the end of the welcome module. Its aim is to measure subjective patient expectations about this treatment. The opinion scale is administered when the patient has completed the treatment, and its aim is to assess satisfaction with this treatment. Our group has used this questionnaire in several research studies [104, 105].

#### Sample size

The data from an RCT using the UP yielded between-group effect sizes of 0.56 for anxiety and 1.11 for depression, as measured with the BAI and BDI-II, respectively [30]. As we aim to compare the intervention with a TAU group, the results of a meta-analysis comparing CBT transdiagnostic treatments versus TAU have also been considered in the estimation of the expected sample size [106]. This meta-analysis reported a medium post-treatment effect size of 0.44 for depression and of 0.34 for anxiety between transdiagnostic treatment protocols vs. TAU conditions. The type of support we provide in this intervention (contact with researchers before, during and after the treatment period) has also been taking into account when estimating the expected sample size, as defined in a previous meta-analysis focused on Internet-based psychological treatments for depression [107]. Based on a power of .80 in a one-tailed test, an alpha of .05, and an estimated drop-out rate of around 30 % [65, 108] we need a sample size of 100 per condition to detect a post-treatment effect size of 0.40 (Cohen’s d) between both groups. Therefore, the total sample size was determined at 200.

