
These modules are sequential, in order to move through the program step by step. The program duration can vary among the users, and it is estimated that for most participants the duration will be 18 weeks. During the study, EmotionRegulation will be accessible only to participants in the online intervention group. Participants will be allowed to use the program at any time they want during the trial period. See Table 2 for other functionalities in EmotionRegulation.

**Table 2 Tab2:** Other functionalities in EmotionRegulation

a) Assessments: The program allows the pre-, post- and follow-up instruments to be completed online.	
b) Module self-assessments: Each module ends with a short list of multiple-choice questions that allow participants to assess their understanding of the module and help them to decide whether they need to review its contents.	
c) Automatic e-mails with reminders when participants have not accessed the program in the past 15 days.	
d) Suicide risk alarms: Therapists receive warnings of participants with high risk of suicide (when participants answer questionnaires that include items assessing high suicide risk)	
e) Post-module questionnaires: Each module includes three brief questionnaires (OASIS, ODSIS and PANAS) to evaluate anxiety, depression and positive/negative affect after each treatment module. Participants are able to monitor these scores in the feedback section through the ‘How am I?’ button.	
f) Printable documents: Each module contains several printable documents (PDF) with summaries and self-monitoring sheets that participants are encouraged to use to practice the skills and strategies.	

Participants in the EmotionRegulation condition will be allowed to maintain medication if there are not changes and/or increases but will not be allowed to receive another psychological treatment during the study period. Failure to fulfill these criteria will result in the participant’s data being excluded from data analysis.

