#### Treatment as usual

Treatment as usual (TAU) is treatment as delivered in current daily practice by psychiatrists and clinical psychologists in the mental health centers in Spain. TAU may refer to psychiatric treatment, which typically includes prescription and monitoring of antidepressant and/or anxiolytic medication, psychological treatment (this may include case management, group psychotherapy, empathic listening and/or supportive counselling), or a combination of both. Patients in the TAU condition already receiving any of the aforementioned treatments are informed they will continue to receive as usual the services received before enrollment in the study.

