#### Analysis

Intention-to-treat analyses and per protocol analyses will be performed. Reporting of the results will follow CONSORT recommendations [75, 76]. First, the two groups will be compared in order to verify that there are no significant differences between them at baseline using samples t-tests for continuous distributed variables and chi-squares test of independence for categorical to confirm that they are comparable after randomization.

The intention-to-treat principle will be used when analyzing primary and secondary post-treatment data and data collected at the 3- and 12-month follow-ups using mixed effect models with full information maximum likelihood estimation. This method has been recommended for its flexibility over repeated-measures ANOVAs to handle missing date more appropriately [109].

Within and between-group changes will be computed calculating standardized effect sizes (Cohen’s d). Cohen’s d is calculated by dividing the differences between means by the pooled standard deviation [110]. An effect size of 0.20 is considered to be small, of 0.50 to be moderate, and 0.80 and above to be large [110].

Per protocol analyses (compliers only analysis) will also be conducted. Despite this procedure suffers from selection bias, it can help to draw conclusions about the maximum treatment efficacy in patients who comply fully with the treatment [111].

As the trial is still in execution, the state of the art regarding analytic methodology for RCT will be reviewed before analyzing the data, thus variations in the selection of the most appropriate analytic procedures may occur.

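### The sample size rests on an unexplained one-tailed 5% test against active care; at two-sided 5% the unadjusted power at d = 0.40 is about 65%, with about 11 points of the shortfall due to the tail and about 4 to the drop-out allowance

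*Protocol article*

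**What the plan says.** The Sample size section gives the only power statement in the article. It specifies "Based on a power of .80 in a one-tailed test, an alpha of .05", adds "an estimated drop-out rate of around 30" per cent, and concludes that 100 patients per condition (200 in total) are needed "to detect a post-treatment effect size of 0.40". The choice of one tail is not explained. The same section cites a meta-analysis of transdiagnostic treatment against TAU with effects of 0.44 for depression and 0.34 for anxiety.

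The Analysis section plans "mixed effect models with full information maximum likelihood estimation" under intention to treat, plus per-protocol analyses and Cohen's d. It does not say whether the tests are one- or two-tailed, and it allows the analytic procedures to be revised before the data are analysed.

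Two other sections bear on the choice of tail. Under Treatment as usual, the comparator may be medication, "psychological treatment (this may include case management, group psychotherapy, empathic listening and/or supportive counselling"), or both. Under Interventions, EmotionRegulation participants "will not be allowed to receive another psychological treatment during the study period". That section and the Eligibility criteria also remove from analysis those in that arm whose medication is changed or increased.

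**The concern.** A one-tailed test at 5% is defensible when a result in the other direction is impossible or of no interest. Neither holds here. The comparison is between a self-administered program with a brief weekly call and whatever specialist care the patient would otherwise receive, and the program arm gives up other psychological treatment. EmotionRegulation could do worse than TAU. Decision makers would need to know that, because the Discussion argues that positive results could reduce face-to-face hours in the public system.

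What is at stake depends on how the outcome tests are run, and the two cases are alternatives:

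- **One-tailed tests.** The chance of falsely claiming benefit is 5% per test, twice the 2.5% that a two-sided 5% test puts in that direction. A difference favouring TAU cannot be declared, however large.
- **Two-sided tests.** The 80% in the Sample size section describes a different test from the one reported, and the trial has less power than its readers are told.

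**Working it through.** **Inputs, all from the Sample size section:** d = 0.40 (SD = 1 on the standardized scale); alpha 0.05 in one tail; power 0.80; 100 enrolled per arm; drop-out about 30%, so 100 × (1 − 0.30) = 70 evaluable per arm. The 1:1 allocation is from Randomization and blinding.

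**Step 1. Reproduce the plan's figure.** For two means, n per arm = 2(z₁₋α + z₀.₈₀)²/d².

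- One-tailed: 2(1.645 + 0.842)²/0.16 = 77.3, rounded up to 78. The t-test calculation also gives 78.
- Allowing for 30% loss by division: 78/0.70 = 111.4, so 112 enrolled per arm.
- Allowing for it by multiplication: 78 × 1.30 = 101.4, so 102.

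The stated 100 is close to the multiplied figure and not to the divided one. Multiplying by 1.30 does not leave 78 after a 30% loss: 102 × 0.70 = 71.

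**Step 2. Power with 70 evaluable per arm at d = 0.40.** By the normal approximation, power = Φ(d√(n/2) − z), with 0.40 × √35 = 2.366.

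- One-tailed: Φ(2.366 − 1.645) = 76.5%. Noncentral t: 76.1%.
- Two-sided: Φ(2.366 − 1.960) = 65.8%. Noncentral t: 65.2%.

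**Step 3. Split the gap between 80% and 65% (noncentral t).**

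| Source | From | To | Points |
|---|---|---|---|
| Drop-out allowance (70 evaluable, 78 needed) | 80% | 76.1% | about 4 |
| One-tailed to two-sided | 76.1% | 65.2% | about 11 |

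**Step 4. What two-sided testing would ask of the design.**

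- 80% power at d = 0.40 needs 2(1.960 + 0.842)²/0.16 = 98.1, rounded up to 99 evaluable per arm (100 by t-test). That is the whole planned sample with no loss. With 30% loss it is 142 to 143 enrolled per arm.
- With 70 evaluable per arm, the effect detectable with 80% power is d = 0.477, above both cited effects against TAU.
- At the cited anxiety effect of 0.34, two-sided power is 51.5%. One-tailed power there is already only about 64%, because 0.34 is below the design effect, so the tail does not account for all of that shortfall.

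**Step 5. Allow for baseline adjustment.** If the model uses the baseline score and the baseline-to-post correlation is r, the residual SD shrinks by √(1 − r²) and the effective d is 0.40/√(1 − r²). The documents give no r, so these values are assumptions. Two-sided 5%, 70 evaluable per arm:

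| r | Effective d | Power |
|---|---|---|
| 0 (unadjusted) | 0.400 | 65% |
| 0.3 | 0.419 | 69% |
| 0.5 | 0.462 | 77% |
| 0.55 | 0.479 | 80% |
| 0.6 | 0.500 | 84% |

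**The case against.** The strongest reply is that the one-tailed assumption is openly disclosed and appears only in the sizing sentence. The aim is superiority over TAU, and every effect cited in support favours the intervention. Sidedness of the outcome tests is a detail that an article may leave to the full protocol or SAP.

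Part of this stands. The silence of the Analysis section is not itself a fault. A reader might infer that the trial will double its false-positive risk and be unable to show harm, and also run at 65% power. The documents do not support that combined reading: the first two follow only from one-tailed outcome tests and the third only from two-sided ones, and the article does not say which will be used. What the reply does not remove is the stated design choice: the protocol chose a tail, gave no reason, and attached its only power claim to it.

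A reader might also blame the whole fall from 80% to 65% on the tail. Step 3 shows that about 4 points are lost to the drop-out allowance whichever tail is used.

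Finally, 65% is the power of an unadjusted t-test on completers, not of the planned mixed models. Those models use all observed scores, and drop-out from the program need not mean a missing outcome. This stands too, and it is why power is better given as a range. It does not restore the stated 80% unless the correlation reaches about 0.55 (with 70 evaluable per arm) or losses are much smaller than planned. With all 100 per arm evaluable, unadjusted two-sided power would be 80.4%.

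**Conclusion.** The concern holds in a conditional form. The trial is sized on an unjustified one-tailed 5% test although the comparator is active care and a worse result with EmotionRegulation is possible and relevant. Either benefit is claimed at 5% one-sided error with no means of declaring a difference favouring TAU, or the stated power describes a test that is not the one reported.

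Under the plan's own 30% loss, unadjusted power at d = 0.40 is about 76% for the one-tailed test and about 65% for the two-sided test. Baseline adjustment could raise the two-sided figure to between 69% and 84% for correlations of 0.3 to 0.6. These figures assume 70 evaluable patients per arm and a single comparison at post-treatment. The correlations are not from the documents. This should be corrected before analysis, but it does not invalidate the trial.

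**What to change.** State in the protocol and SAP that the confirmatory tests on BAI and BDI-II are two-sided at 5% and reported with 95% confidence intervals. Keep N = 200. Restate two-sided power at d = 0.40 with 70 evaluable per arm as about 65% unadjusted, or about 69% to 84% with baseline adjustment for an assumed correlation of 0.3 to 0.6 (77% at 0.5). Mention separately that 80% power for the one-tailed calculation needed 78 evaluable, hence about 112 enrolled, per arm.

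The cost is wording only: no extra patients and no change to treatment or assessments. The article reports the trial as still recruiting, so the change can be made before the data are analysed. The downside is that the stated power becomes less favourable. The change makes the power claim honest but does not restore 80% unadjusted, which would take 142 to 143 enrolled per arm.

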### Randomization and blinding

Patients will be randomly allocated in a 1:1 ratio to either of the two groups (EmotionRegulation or TAU) using a computer-generated random number sequence. The Epidat 4.1 program will be used to generate this sequence. The allocation will be carried out by an independent researcher who will be unaware of the characteristics of the study. The sequence will be concealed until interventions are assigned. Patients will agree to participate before the random allocation and without knowing to which treatment they will be allocated. Study researchers conducting psychological assessments (that is, diagnostic interviews) throughout the entire study will be masked to the participants' treatment conditions and unaware of the treatment group to which the patient belongs. For ethical and practical reasons, participants will not be blind to the treatment conditions.

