Finally, a number of potential limitations should be indicated. First, dropout rates are expected to be high (around 30 %) [67, 110]. Efforts to maintain these drop-out rates below this percentage will be made by providing human support (before, during, and after the intervention) and ICT-support (for example, emails and mobile phone text messages). Second, negative attitudes towards Internet interventions by both clinicians and patients may affect recruitment as well as dropout rates. To minimize the effect of negative attitudes, the nature and characteristics of the intervention will be explained to clinicians involved in the trial. Moreover, for this purpose they will be given a handbook with relevant information about the study (for example objectives of the study, study design, and characteristics of the intervention). In order to increase participant’s credibility, prior to enrollment they will be given a sheet with relevant information concerning the characteristics and objectives of the study, and other issues related to ethics, voluntary participation and confidentiality of the data. Finally, other difficulties could be problems with recruitment, as many people who attend public mental health units do not have access to the Internet at home.

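### The stated inputs require 112 per arm, not 100: after 30% drop-out, 100 per arm gives about 76% power at d = 0.40, not 80%

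*Protocol article*

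**What the plan says.** The Sample size section gives all the inputs to a two-group comparison of post-treatment means. The test is fixed by "Based on a power of .80 in a one-tailed test, an alpha of .05", the loss by "an estimated drop-out rate of around 30" per cent, and the conclusion is "we need a sample size of 100 per condition to detect a post-treatment effect size of 0.40", expressed as Cohen's d, for a total of 200. The Randomization and blinding section confirms equal allocation: "Patients will be randomly allocated in a 1:1 ratio to either of the two groups". The Discussion repeats the loss assumption, saying that "dropout rates are expected to be high" and again giving around 30%.

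The design value of 0.40 follows a short review of evidence. A trial of the Unified Protocol is cited for between-group effects of 0.56 on the BAI and 1.11 on the BDI-II. A meta-analysis against treatment as usual (TAU) is cited next: "This meta-analysis reported a medium post-treatment effect size of 0.44 for depression and of 0.34 for anxiety". A further meta-analysis is cited on the type of support provided. The sample-size text mentions no baseline adjustment and no gain from repeated measures.

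**The concern.** Because every input is stated, the result can be checked directly, and 100 per condition looks too small. After 30% loss it leaves 70 per arm, fewer than a one-tailed test at d = 0.40 needs for 80% power. Readers will use this paragraph to judge what the trial could detect, and it promises more power than its own assumptions deliver.

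**Working it through.** **Inputs.** From Sample size: d = 0.40 (so SD = 1), one-tailed alpha .05, power .80, drop-out 30%. From Randomization and blinding: 1:1 allocation.

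**Step 1: evaluable participants per arm.**
n = 2(z₁₋α + z₁₋β)² / d² = 2(1.645 + 0.842)² / 0.40² = 77.3 by the normal approximation. The noncentral t gives 77.97. Both round up to 78.

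**Step 2: allowance for drop-out.**
If 30% are lost, 70% of those randomised remain, so the number to randomise is n / (1 − 0.30) = 78 / 0.70 = 111.4, that is 112 per arm and 224 in total. The stated 100 per arm and 200 in total are not reproduced.

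**Step 3: routes that come close to 100.**
- Multiplying by 1.30 instead of dividing by 0.70: 77.3 × 1.30 = 100.5 from the unrounded figure, or 78 × 1.30 = 101.4 from the rounded one.
- A two-tailed test with no drop-out allowance: 99 per arm by the normal approximation, 100 by the noncentral t (99.08 rounded up), with 80.4% power at 100 per arm.

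Neither is the calculation the section describes, and the article does not show whether either was used.

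**Step 4: what 100 per arm delivers.**
Evaluable per arm: 100 × 0.70 = 70. By the normal approximation, one-tailed power is Φ(d√(n/2) − 1.645) = Φ(0.40 × √35 − 1.645) = Φ(0.72) = 76.5%. The noncentral t gives 76.1%.
- Effect detectable with 80% power at 70 per arm: d = 0.422.
- Largest drop-out at which 100 per arm still leaves 78: 1 − 78/100 = 22%.

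**Step 5: power with 70 per arm across the cited effects (one-tailed .05, noncentral t).**

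| Effect | Source given in the section | Power |
|---|---|---|
| 0.34 | anxiety, meta-analysis versus TAU | 64% |
| 0.40 | design value | 76% |
| 0.44 | depression, meta-analysis versus TAU | 83% |
| 0.56 | BAI, Unified Protocol trial | 95% |

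**Step 6: possible gain from baseline information.**
If the analysis uses the baseline score, the residual SD falls by the factor √(1 − r²), where r is the correlation between baseline and post-treatment scores. The article gives no r, so these values are assumptions. Normal approximation, 70 per arm, d = 0.40, one-tailed:

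| r | Power |
|---|---|
| 0.3 | 79.8% |
| 0.4 | 82.6% |
| 0.5 | 86.2% |

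**The case against.** Three arguments can be made in the plan's favour.

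- **The shortfall is small and depends on the loss.** The article says around 30%, and the Discussion describes efforts to keep drop-out lower. At 22% the stated power would be met. This limits the consequence and stands as a reason for moderate severity. It does not repair the calculation, which is made at around 30%.
- **The calculation is simpler than the planned analysis.** The Analysis section plans mixed models with full information maximum likelihood, which can use incomplete cases and repeated measures. A modest correlation would recover the lost power. This also stands, and it tells against inferring that the trial will in fact be underpowered. But the sample-size text does not rely on any such gain.
- **The choice of 0.40 is a judgement.** A reader might infer that the plan also makes an error by not powering the BAI, a primary outcome, at 0.34. The document does not support that. It never claims 80% power at 0.34. It cites two anxiety effects, and ties the BAI by name only to 0.56, where power is 95%. The 0.34 was measured against TAU and so matches this comparator, which makes it a sensible sensitivity value, but it is not the plan's assumption. The section also draws on a third source, on support, whose figures it does not give.

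A reader might also take multiplication by 1.3 as the established cause. It is one possibility among at least two.

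**Conclusion.** The sample-size statement is wrong as written. Its own inputs require 78 evaluable and 112 randomised per arm (224 in total), which is 12 per arm more than stated. At 100 per arm, power at d = 0.40 is about 76%, roughly 4 points below the claim. This rests on the stated one-tailed test, a 30% loss in each arm, and a comparison of post-treatment means without baseline adjustment, which is all the section describes. The finding does not depend on how the figure of 100 arose. Severity is moderate: a stated figure needs correcting, but the shortfall is modest and the planned model may make it up. The spread from 64% to 95% across the cited anxiety effects is useful information for readers, not a second error.

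**What to change.** Keep the total of 200 and correct the Sample size text in one of two ways:

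1. State that 100 randomised per arm leaves 70 evaluable at 30% drop-out, giving 76% one-tailed power at d = 0.40, with 80% power at d of about 0.42.
2. Justify 80% through the planned mixed model, stating the assumed correlation between baseline and post-treatment scores and its source. A value of about 0.3 gives roughly 80% at d = 0.40 with 70 per arm.

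In either case, add the power with 70 per arm at 0.34, 0.44 and 0.56, labelled by source and presented as a sensitivity range.

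The cost is a text correction with no extra participants, which suits a trial that is already recruiting. Under the first option the stated power becomes slightly less favourable.
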